### Exploring the physiological impact

Autonomic functions will be assessed using heart rate variability (HRV) analysis. A chest belt capable of measuring heart rate and inter-beat interval (IBI) will be used at baseline and after the end of treatment. Measurements and calculations of analysis parameters will be done according to relevant standards and guidelines [39, 40]. Several HRV parameters can be indicative of a change in autonomous status. Since all of these are based on measured IBI, we will explore a range of parameters and compare results to existing data where such data exist.

### Participant timeline

Eligible participants will be identified by clinicians working at the respective trial sites. They will ask the families whether they are willing to be contacted by the trial researchers for further information. The trial researcher will send a letter of information and request permission to follow-up with a phone call. Following the phone call, an in-person meeting will be scheduled, in which both oral and further written information will be provided. If the families wish to participate, a second in-person meeting is scheduled. At this second meeting, informed consent is obtained as well as a standard diagnostic—and health evaluation alongside baseline assessment and HRV measurements. The child is finally included in the trial, granted they meet the inclusion criteria following the health – and diagnostic evaluation. Randomisation then commence, in which the participant is allocated to either active or sham eTNS.

They will then proceed to test the device for four weeks. Families will keep a logbook for daily reporting on how the previous night had gone by. Once a week, they will fill in an online questionnaire received by email related to the primary exploratory outcome and the reporting of any adverse events. This email will also contain questions regarding the use of the device and concomitant medication. In addition, the families will receive a weekly phone call from the trial researcher, to remind them to fill in the questionnaire and to allow the families to ask questions if needed. Families may also contact a trial researcher directly via phone throughout the trial period.

Following the four weeks, an in-person meeting is scheduled, in which the families and trial investigators meet to discuss and share their experience. During this meeting, exploratory outcomes will once again be assessed, alongside HRV measurements and the rating of any adverse events. The full participant timeline is seen in Fig. 1.

**Fig. 1 Fig1:**
[figure not shown]
Participant timeline

### Sample size and power consideration

We will include 60 participants which corresponds to approximately 20% of the sample size needed for the full-scale randomized superiority trial. This corresponds to a power of 48% for the primary outcome (ADHD core symptoms) in this feasibility trial, indicating that the risk of type 1 error is high, and any finding thus may only be considered as exploratory.

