### Randomisation and blinding

The randomization procedure will be computer-based and provided by The Copenhagen Trial Unit (CTU). The allocation sequence generation will be performed using block sizes of varying lengths concealed for the investigators. Randomization will be stratified by use of ADHD medication compared to no use of ADHD medication at entry. The allocation ratio will be 1:1. Both participants, personal and outcome assessors will be blinded to treatment allocation. Only one investigator will have access to group assignments. This investigator will also be the main person involved with any technical difficulties the families may experience during the trial. Premature disclosure of blinding may occur in case of adverse events where unblinding in considered essential for the safety and further treatment of the patient.

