### Data analysis

Baseline characteristics will be reported and described using descriptive statistics. Continuous outcomes will be analysed by linear regression and dichotomous outcomes will be analysed using logistic regression. In the primary analysis we will include the intention-to-treat population, i.e. all randomised participants will be included in the analysis in the group to which they were randomised, even when they have received only part of the intervention. The analyses will be adjusted for the stratification variables used in the randomisation. Before the randomisation of the last participant, we will develop and publish a detailed statistical analysis plan with a detailed description of the analyses.

Statistical analyses will be performed by two blinded statisticians presenting independent reports. Our patient population includes both treatment-naïve patients as well as those already exposed to medication. In this feasibility and pilot trial, we will assess the collective effect across all patients included. We will not investigate the effect of intervention based on medication status. Such subgroup analysis will, however, be conducted in the later, larger randomised trial. A data monitoring committee will also be included in the future, larger trial.

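### The protocol reads 48% power as a high type 1 error risk when it is a 52% type 2 error risk, and its 20% and 48% figures do not reconcile under a conventional design with common inputs

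*Protocol article*

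**What the plan says.** The section on sample size and power consideration in the protocol article consists of two sentences. The first sets the size, "We will include 60 participants", and says that this "corresponds to approximately 20% of the sample size needed for the full-scale randomized superiority trial". The second says: "This corresponds to a power of 48% for the primary outcome (ADHD core symptoms) in this feasibility trial". It then draws the inference "indicating that the risk of type 1 error is high, and any finding thus may only be considered as exploratory".

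Elsewhere the article fixes the design features needed for a check. Under randomisation and blinding: "The allocation ratio will be 1:1". Under data analysis: "Continuous outcomes will be analysed by linear regression and dichotomous outcomes will be analysed using logistic regression", adjusted for the stratification variable. The article gives no alpha, effect size, SD or target power for either trial, and it does not print the full-trial sample size as a number.

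**The concern.** There are two separate problems.

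**The error type.** The text infers a high type 1 error risk from low power. Low power is, by definition, a high type 2 error risk. The sentence therefore warns readers about positive findings on the wrong ground and does not name the risk that 48% power does create: a real effect on ADHD core symptoms is about as likely to be missed as found.

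**The two figures.** The second sentence opens by linking the 48% to the 60 participants that are about 20% of the full trial. A trial one fifth the size of a conventionally powered trial would usually have well under 48% power for the same effect. If the figures come from one calculation, then either the power of this trial or the size of the full trial appears to be misstated. This is the only sizing statement in the article, and the trial's declared purpose is to prepare that larger trial.

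**Working it through.** **1. Error type (no assumptions needed)**

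Type 2 error = 1 − power = 1 − 0.48 = 0.52. The type 1 error equals alpha whatever the sample size.

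**2. Inputs for the consistency check**

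- N = 60, ratio 1:1, so 30 per arm (stated).
- Fraction of the full trial about 0.20 (stated), so full N ≈ 60 / 0.20 = 300.
- Power at N = 60 is 48% (stated).
- Alpha two-sided 0.05: assumed.
- Full-trial power 80–90%: assumed as conventional.
- Same effect and SD in both trials, simple two-group comparison of means: assumed.

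The 48% cannot be rebuilt from stated inputs, because the effect and alpha are missing. Taken alone, it is what a standardised difference of d = 0.50 gives at 30 per arm: 47.8% by the exact noncentral t, 49.1% by the normal approximation.

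**3. From the 20% to the power**

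With common effect, SD and alpha, the noncentrality scales with the square root of N and the effect cancels:

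power at 60 = Φ( √0.20 × (z_α + z_power) − z_α ), with √0.20 = 0.447 and z_α = 1.960.

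| Full-trial power | Calculation | Power at N = 60 | Exact t |
|---|---|---|---|
| 80% | 0.447 × (1.960 + 0.842) − 1.960 = −0.707 | 24.0% | 23.5% |
| 90% | 0.447 × (1.960 + 1.282) − 1.960 = −0.510 | 30.5% | 29.8% |
| 95% | 0.447 × (1.960 + 1.645) − 1.960 = −0.348 | 36.4% | 35.6% |
| 99% | 0.447 × (1.960 + 2.326) − 1.960 = −0.043 | 48.3% | – |

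The effects behind the exact values are d = 0.325 (80% power at N = 300) and d = 0.376 (90%).

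**4. From the 48% to the fraction**

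At d = 0.50 and two-sided 5%, the exact t requires 128 in total for 80% power and 172 for 90%. Then 60/128 = 47% and 60/172 = 35%, against the stated 20%. The effect that gives exactly 48% at 60 (d = 0.501) has 99.1% power at 300.

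**5. Sensitivity, with full-trial power kept at 80–90%**

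| Variation | Power at N = 60 |
|---|---|
| One-sided 5% in both trials | 30–37% |
| Fraction 25% instead of 20% | 29–37% |
| Full N inflated for 10–25% dropout | 26–39% |

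None reaches 48%.

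**6. Inputs under which the pair would fit**

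- Full-trial power of about 99% (48.3%, above).
- A smaller effect assumed for the full trial: d about 0.32–0.38 there, against about 0.50 here.
- A stricter full-trial alpha with attrition: d = 0.50, two-sided 0.01 and 90% power need 242 analysed; with 20% dropout 242 / 0.80 ≈ 303, so 60 is 20%.
- Sizing each of two medication strata at d = 0.50: 2 × 128 = 256 to 2 × 172 = 344, so 60 is 23% to 17%.
- A looser alpha here: two-sided 0.20, with the full trial at 80% power and two-sided 5%, gives 48.9%.

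**The case against.** Nobody can defend the term type 1 as an inference from power. The nearest rescue is that the many exploratory outcomes inflate the family-wise type 1 error, or that a significant result from an underpowered trial is less likely to be true. Both are real issues, but they are different from the one stated: the sentence derives the risk from the power figure alone.

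The objection to the second part is stronger. The contradiction appears only after one supplies an alpha, a full-trial power, a common effect and a simple two-group design, none of which is stated. A reader might infer that the figures can agree only if the full trial has 99% power, or that one of them has been shown to be false. The document supports neither reading. Several other sets of inputs reconcile the pair, as step 6 shows, and one has some footing in the text: the data analysis section says that subgroup analysis by medication status is left to the larger trial, so sizing by stratum is conceivable, although it is nowhere stated. An article may also leave the full derivation to the full protocol, so the missing inputs are not in themselves a fault.

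On severity, the objective is feasibility, the feasibility outcomes have their own criteria, and the clinical outcomes are called exploratory and preliminary in several sections. The sentence's practical conclusion, that findings are exploratory only, stays right once the error type is corrected. The 48% itself is printed, so the power is not hidden.

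What survives is the plain misstatement of the error type, and a pair of linked figures that ordinary assumptions do not reproduce.

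**Conclusion.** The first part holds without conditions: the stated 48% power is a 52% type 2 error risk and says nothing about the type 1 rate. Its main consequence is that a null result on ADHD core symptoms would be uninformative.

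The second part holds conditionally. For a two-group design with the same effect, SD and two-sided 5% alpha in both trials, and 80–90% power in the full trial, the figures differ by a wide margin: about 24–30% power instead of 48%, or about 35–47% of the full trial (128–172 in total) instead of 20%. If the 20% stands on that basis, the type 2 error here is about 70–76%. This shows that the pair does not reconcile under ordinary assumptions. It does not show which figure is wrong, or that either must be.

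Severity: should-fix. No feasibility criterion depends on the sentence, and the clinical outcomes are already exploratory.

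**What to change.** - Replace type 1 with type 2 and give its size (52% if the 48% stands).
- Add that absence of a difference in ADHD core symptoms will not be read as absence of effect.
- Recheck the 20% and the 48% against one set of inputs (effect, SD, alpha, full-trial power). Correct whichever fails, or state in a clause the basis on which the two differ, for example a different effect, alpha or stratum-wise sizing in the full trial.

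The cost is a change of wording and one recalculation. No participants, procedures, analyses or feasibility criteria change, although a stated figure may become less favourable.

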### Randomisation and blinding

The randomization procedure will be computer-based and provided by The Copenhagen Trial Unit (CTU). The allocation sequence generation will be performed using block sizes of varying lengths concealed for the investigators. Randomization will be stratified by use of ADHD medication compared to no use of ADHD medication at entry. The allocation ratio will be 1:1. Both participants, personal and outcome assessors will be blinded to treatment allocation. Only one investigator will have access to group assignments. This investigator will also be the main person involved with any technical difficulties the families may experience during the trial. Premature disclosure of blinding may occur in case of adverse events where unblinding in considered essential for the safety and further treatment of the patient.

### Data management

Data will be collected using electronic case report forms (eCRFs) and handled using REDCap (Research Electronic Data Capture) [41, 42].

### Data analysis

Baseline characteristics will be reported and described using descriptive statistics. Continuous outcomes will be analysed by linear regression and dichotomous outcomes will be analysed using logistic regression. In the primary analysis we will include the intention-to-treat population, i.e. all randomised participants will be included in the analysis in the group to which they were randomised, even when they have received only part of the intervention. The analyses will be adjusted for the stratification variables used in the randomisation. Before the randomisation of the last participant, we will develop and publish a detailed statistical analysis plan with a detailed description of the analyses.

Statistical analyses will be performed by two blinded statisticians presenting independent reports. Our patient population includes both treatment-naïve patients as well as those already exposed to medication. In this feasibility and pilot trial, we will assess the collective effect across all patients included. We will not investigate the effect of intervention based on medication status. Such subgroup analysis will, however, be conducted in the later, larger randomised trial. A data monitoring committee will also be included in the future, larger trial.

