### Inclusion criteria

7 to 17 years of age at the time of trial enrolment.A clinical diagnosis of ADHD according to criteria for ICD-10: F90.0, F90.1, F90.8, F98.8C [25].The ADHD diagnosis must be verified by the Diagnostic and Statistical Manual for Mental Disorders (DSM-5) [26] using The Schedule for Affective Disorders and Schizophrenia for School-aged Children (K-SADS) [27].A total score above 24 on the ADHD rating scale (ADHD-RS) at baseline.Signed informed consent from parents/legal caretakers and from the patients aged ≥ 15.

We will include treatment-naïve patients, patients who previously have received stimulant medication, and patients in stable, ongoing stimulant medication (methylphenidate or dexamphetamines/lisdexamphetamine) during the time of the trial.

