#### Primary exploratory outcome

ADHD core symptoms—measured by the ADHD-IV rating scale (parent- and teacher rated) [31]. Parent ratings will be assessed at baseline, weekly, and at end of treatment. Teacher ratings will be assessed at baseline and at end of treatment.Absence from school – measured as total hours of absence reported by logbook (parents) and through direct contact with the teachers.

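### The adjustment stated for the linear regressions names the medication stratum but not the baseline score, and following it as written would give up precision that costs nothing to obtain

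*Protocol article*

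**What the plan says.** The Data analysis section of the protocol article sets the model: "Continuous outcomes will be analysed by linear regression and dichotomous outcomes will be analysed using logistic regression". It sets the adjustment: "The analyses will be adjusted for the stratification variables used in the randomisation". Under Randomisation and blinding there is a single stratification factor with two levels: "Randomization will be stratified by use of ADHD medication compared to no use of ADHD medication at entry".

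The baseline data exist. Entry requires "A total score above 24 on the ADHD rating scale (ADHD-RS) at baseline", so every randomised child should have a baseline ADHD-RS total. The Exploratory outcomes section schedules the clinical outcomes at baseline and at four weeks. For the primary exploratory outcome, "Parent ratings will be assessed at baseline, weekly, and at end of treatment", and "Teacher ratings will be assessed at baseline and at end of treatment".

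The analysis population is intention-to-treat: "all randomised participants will be included in the analysis in the group to which they were randomised". The detail is deferred: "Before the randomisation of the last participant, we will develop and publish a detailed statistical analysis plan with a detailed description of the analyses".

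**The concern.** The article does more than announce a later plan. It names a method and a set of adjustment variables, and the baseline value of the outcome is not among them. For a symptom scale rated before and after four weeks, that value is likely to be the strongest predictor of the final score. Medication use at entry, a yes/no factor, is a weak substitute.

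Two things are at stake if the set is carried forward as written. The treatment estimate has a larger standard error than the collected data allow. And any chance difference between the arms in baseline severity passes into the estimate in proportion to the baseline to week-4 correlation. Both matter more in a trial of 60 than in a large one. The trial is also meant as the pilot for a larger study, which a noisier estimate informs less well.

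**Working it through.** **Inputs from the article.** 60 participants, 1:1 allocation, hence 30 per arm; power 48% for ADHD core symptoms; 60 described as about 20% of the full trial, hence about 60/0.20 = 300.

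**Inputs not in the article (assumed).** Two-sided 5% test; correlation r between baseline and week-4 score of 0.3 to 0.7; 48% taken first as an unadjusted figure.

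**1. The stated 48%.** It cannot be reproduced from the article, which gives no effect size, SD, significance level or full-trial power. If 300 gives 80% to 90% power (two-sided 5%), then 60 gives only 24.0% to 30.5%. Solving backwards from 48%:

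d = (z₀.₉₇₅ + z₀.₄₈)/√(n/2) = (1.960 − 0.050)/√15 = 0.493.

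An assumed d of 0.5 gives 49.1% by the normal approximation and 47.8% by the t-test. So 48% is compatible with an unadjusted two-sample comparison at d = 0.5, but nothing in the article confirms that this was its basis.

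**2. Effect of adding baseline.** Residual variance is multiplied by 1 − r². Power = Φ(d√15/√(1 − r²) − 1.960), with d√15 = 1.910. The equivalent unadjusted sample size is 60/(1 − r²).

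| r | Variance reduction | Power at N = 60 | Equivalent unadjusted N |
|---|---|---|---|
| 0 | 0% | 48.0% | 60 |
| 0.3 | 9% | 51.7% | 66 |
| 0.5 | 25% | 59.7% | 80 |
| 0.7 | 49% | about 76% | 118 |

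Example, r = 0.5: 1.910/0.866 − 1.960 = 0.245, and Φ(0.245) = 59.7%.

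The entry rule of a total above 24 restricts the baseline range and may lower r. At r = 0.2 the gain is small: variance down 4%, power 49.6%.

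**3. If 48% already assumed baseline adjustment.** The gains in step 2 then do not apply. Instead, a model without baseline would have Φ(1.910·√(1 − r²) − 1.960) = 44.5%, 38.0% or 27.6% at r = 0.3, 0.5 or 0.7.

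**4. Chance imbalance.** With 30 per arm, the standard error of the baseline difference is √(2/30) = 0.26 SD. An imbalance of that size shifts an estimate without baseline by r × 0.26, that is 0.08, 0.13 or 0.18 SD at r = 0.3, 0.5 or 0.7, against the back-solved effect of 0.49 SD.

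**5. What the weekly parent ratings could add.** If a fraction m of week-4 scores is missing, and earlier ratings explain a share R² of the week-4 variance, using them multiplies the variance by 1 − mR² relative to observed week-4 scores alone. For R² from 0.25 to 0.7 (assumed), the reduction is 2.5% to 7% at m = 10% and 6% to 17.5% at m = 25%. At m = 0 it is zero.

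**The case against.** The strongest reply is that the article is an outline. It promises a detailed plan before the last randomisation, and that plan may well include baseline. The article does not say that the stratum is the sole covariate and does not rule baseline out. This stands, and it is why the point concerns what would follow from the stated set, not a proven omission from the final analysis. It does not remove the point: an adjustment set has been published, and a plan that follows it would carry the gap forward.

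The second reply is that the power figures rest on inputs that the article lacks: the correlation, and whether 48% is unadjusted. This also stands. The direction of the gain does not depend on the second input, but its size depends on the first.

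The third is that little hangs on it. The objective is feasibility, the clinical outcomes are exploratory, and none of the feasibility benchmarks depends on an efficacy test. This sets the priority.

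A reader might go further and infer that children without a week-4 score will be dropped, so that the intention-to-treat statement is contradicted. The article does not support that. It states no complete-case rule, says that all randomised participants are included, and leaves missing-data handling to the later plan. Linear regression can be combined with imputation. The 90% and 75% completion figures are feasibility benchmarks, not an accepted level of missing data. Nor does it follow that a repeated-measures model is required: the weekly ADHD-RS ratings come from parents only, they add nothing to the week-4 contrast when data are complete, and the choice between such a model and imputation is a matter of preference.

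**Conclusion.** The point holds as one about precision. The published adjustment set leaves out the baseline score, which is already collected, and an analysis confined to that set would be less efficient and more exposed to chance baseline imbalance.

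The variance at stake is 9% to 49% for an assumed correlation of 0.3 to 0.7, possibly nearer the lower end because of the entry threshold. The corresponding power, about 52% to 76% instead of 48%, holds only if 48% was computed without baseline adjustment. No conclusion about excluded children or a breach of intention-to-treat is drawn. This is a worthwhile improvement of modest priority, since it affects exploratory outcomes only.

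**What to change.** In Data analysis, extend the adjustment sentence along these lines: each continuous outcome measured at baseline is analysed by linear regression with its own baseline value and the medication stratum as covariates. If the statistical analysis plan already says this, the sponsor need only confirm it.

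Optionally, that plan can say how the weekly parent ADHD-RS ratings will be used where week-4 scores are missing, by a repeated-measures model or by imputation. Teacher ratings, taken only at baseline and end of treatment, stay with the single-time-point regression including baseline.

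The cost is wording, plus one degree of freedom per model. No new data, visits or participants are needed. The change should be fixed before unblinded results are seen.

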The mechanism of action in ADHD remains to be fully investigated, yet it is hypothesised that eTNS may improve ADHD symptomatology by activating the fronto-basal ganglia circuit [9]. In accordance, McGough et al. [16] reported that the reduction in ADHD core symptoms following eTNS was associated with increased activation of frontal brain regions. Such change in cortical activity is similar to the mechanism thought to underlie successful pharmacological treatment for ADHD, and the localisation matches with the areas considered involved in the neuropathology of ADHD [17]. In addition, it is hypothesised that the therapeutic effect of eTNS may involve a regulation of neurotransmitters such as dopamine, and a potential induction of long-term potentiation [17, 18]. If this is in fact the case, eTNS may not only mimic the action of medicine such as methylphenidate, but also have the potential of inducing long-lasting effects within the targeted neuronal network.

The Monarch eTNS device is designed to be easily controlled by the parents at home, with stimulation being applied during night-time. This level of convenience and minimal interference of the intervention on daily activities, may be appealing to some families. In the preliminary study by Lykke Huus et al. [19], we tested the Monarch eTNS device on four children in Denmark. The study was approved by the Research Ethics Committee in Region Zealand (SJ-855). Parents generally considered the Monarch eTNS device to be user-friendly and they felt confident managing the device following the information they received prior to the study. The acceptance from the children varied, yet they were generally positive. No serious adverse events were observed.

We aim to assess the feasibility of and pilot a larger randomized clinical trial investigating the Monarch eTNS device for patients aged 7 to 17 years with ADHD in Denmark. If this Danish project shows feasibility, we will follow up with a full-sized randomised clinical trial comparable to the ongoing trials in UK [20] and US [21]. In the present trial, initial steps will be taken to explore the impact on the autonomic nervous system using heart rate variability measurements.

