#### Outcomes

### Feasibility outcomes

Feasibility outcomes will be measured at the end of the 4-week treatment period.The proportion of participants assessed for eligibility who consent to inclusion and randomizationWe will compare the number of eligible participants to the number of randomized participants. We will accept a difference above 50% (95% CI 40.2% to 59.6%). A larger difference can impose difficulties with recruitment in a future randomized trial.Compliance with the interventionWe will calculate the number of participants fulfilling treatment for both the group receiving sham and active eTNS. Compliance with treatment will be defined as completing the treatment in 70% (95% CI 58.4% to 81.6%) of the nights during the four weeks. Abruption of treatment can only be accepted if it happens within less than four nights in a row.Acceptability of the interventionThe acceptability of the intervention will be assessed using a semi-structured qualitative interview guide with predefined questions:How did you feel about administering and controlling the device?How did your child feel about receiving this type of treatment?How was it for your child to receive home-treatment with the device in addition to other strategies provided by the clinic?Did the intervention have any influence on the relationship between your child and the parents/siblings/school/friends?Completion of follow upCompletion of follow-up will be defined as completing the assessment of the primary exploratory clinical outcome at the end of the intervention. The number of participants with completed outcomes will be compared to the number of participants in total. If the number of participants completing this assessment is above 90% (95% CI 82.4% to 97.6%), this will be acceptable for a future full-size trial. If the number of participants completing the assessment is below 75%, this will introduce serious problems with the interpretation of the results.Use of concomitant treatmentAny concomitant treatment or changes in medication will be assessed for each participant and subsequently evaluated for the two groups at the end of the trial.

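### Several feasibility criteria are contradictory or open, and the analysis plan that could settle them may be fixed when the pooled counts are nearly final and visible without unblinding

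*Protocol article*

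**What the plan says.** **Timing.** Data analysis: "Before the randomisation of the last participant, we will develop and publish a detailed statistical analysis plan". The same section relies on blinding: "Statistical analyses will be performed by two blinded statisticians presenting independent reports".

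**What the trial decides.** Its objective is feasibility, and the clinical outcomes are exploratory. Background states the consequence: "If this Danish project shows feasibility, we will follow up with a full-sized randomised clinical trial".

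**What the team sees as the trial runs.** Families keep a nightly logbook (Records of intervention). They also get a weekly online questionnaire and a weekly call from the trial researcher (Participant timeline). Of the weekly e-mail the article says: "This email will also contain questions regarding the use of the device and concomitant medication".

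**What is already fixed.** Under Feasibility outcomes, "Feasibility outcomes will be measured at the end of the 4-week treatment period". That section gives a 50% figure for consent, defines compliance as 70% of nights, and defines completion as having the primary exploratory outcome assessed. Completion above 90% is acceptable and below 75% is a serious problem. Discontinuation or modification of interventions adds that a night counts from five hours of uninterrupted stimulation.

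**What is contradictory or open.**
- *Consent.* Feasibility outcomes accepts a gap between eligible and randomised participants that exceeds 50%, then says that a larger gap would hamper recruitment. The outcome's title counts everyone assessed for eligibility, while its text counts the eligible.
- *Interruptions.* Feasibility outcomes and Discontinuation or modification of interventions limit consecutive missed nights to fewer than four. The Discussion limits missed nights to fewer than four over the four weeks, without saying that they are consecutive.
- *Compliance.* No share of participants who must comply is stated.
- *Completion.* Feasibility outcomes requires strictly more than 90%, while the Discussion accepts exactly 90% as well. Neither gives a verdict between 75% and 90%.

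**The concern.** Fixing an analysis plan before the last randomisation protects comparisons that need the treatment code, because nobody can see the contrast when the rules are written. It does not protect totals over all participants. The consent share, completion and pooled compliance need no code and can be tallied by the team at any time. Blinded statisticians do not change that.

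This would not matter if every criterion had one reading. Where two sections disagree or a rule is absent, a later document can adopt either reading and still claim to follow the protocol. If that choice is made when the counts are nearly complete, the feasibility verdict, and with it the decision on a full-size trial, can depend on which reading was picked.

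**Working it through.** **1. The protocol's own figures.** The planned size is 60: "We will include 60 participants which corresponds to approximately 20% of the sample size needed for the full-scale randomized superiority trial". The Wald interval is p ± 1.96 × √(p(1−p)/n). With n = 60:
- p = 0.70: half-width 1.96 × √(0.21/60) = 0.116, so 58.4% to 81.6%, as printed beside compliance.
- p = 0.90: half-width 1.96 × √(0.09/60) = 0.076, so 82.4% to 97.6%, as printed beside completion.
- p = 0.50 is printed with 40.2% to 59.6%. No denominator is given and no interval tried matched both ends: Wald with n = 100 gives 40.2% to 59.8%, and Wilson with n = 100 gives 40.4% to 59.6%.

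The compliance interval uses n = 60, so it treats 70% as a share of participants. The text beside it defines 70% as a share of one participant's nights. The participant-level target is therefore open.

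**2. What is known at the latest permitted date.** Up to 59 of 60 are randomised. The article gives no recruitment period, so assume even recruitment over m months. Children still within their 28 days number 60 × 28/(m × 30.44), and those finished number 59 minus that.

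| m (assumed) | still in treatment | finished | share of 60 |
|---|---|---|---|
| 6 | 9.2 | 49.8 | 83% |
| 12 | 4.6 | 54.4 | 91% |
| 18 | 3.1 | 55.9 | 93% |
| 24 | 2.3 | 56.7 | 94.5% |
| 36 | 1.5 | 57.5 | 96% |

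The consent share is known except for the last inclusion. If 118 had been eligible (assumption), it would move from 59/118 = 50.0% to 60/119 = 50.4%.

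**3. Whether the reading changes the verdict.**

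*Completion.* 54/60 = 90.0%. This is not above 90%, so Feasibility outcomes would need 55/60 = 91.7%, but it satisfies the Discussion. Since 45/60 = 75%, results from 45 to 54 have no stated verdict under Feasibility outcomes, and 45 to 53 have none under the Discussion.

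*Interruptions.* 70% of 28 nights is 19.6, so 20 nights are needed and up to 8 may be missed if no run reaches four (rule A). The Discussion, read as a total, allows 3 missed nights, so at least 25 of 28, or 89% (rule B). If each night is missed independently (assumption), simulation of 200,000 participants gives:

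| nightly use | compliant, rule A | compliant, rule B |
|---|---|---|
| 80% | 89% | 16% |
| 85% | 97.5% | 38% |
| 90% | 99.7% | 69% |
| 95% | 100% | 95% |

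*Consent, direction.* If the share randomised must exceed 50%, the gap must be below 50%. The literal sentence accepts a gap above 50%. These give opposite verdicts on any result other than exactly 50%.

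*Consent, denominator.* With 60 randomised, a share above 50% needs fewer than 60/0.5 = 120 in the denominator. A trial with fewer than 120 eligible but 120 or more assessed would pass on one denominator and fail on the other.

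**The case against.** The strongest objection is that the protocol has already fixed most of this. The 70%-of-nights definition, the five-hour night, the definition of completion and the 90% and 75% limits are published, and altering them later would be a visible deviation. This stands. A reader might infer from the late deadline that all feasibility definitions and limits can be set with the answer known. The article does not support that, and the point is confined to the criteria listed above.

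It also stands that not every feasibility outcome is an open count. Acceptability comes from a qualitative interview. Compliance is to be calculated by arm, so blinding does protect the arm-specific figures and leaves only the pooled total visible. Concomitant treatment is evaluated by group.

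A further objection is that the article gives a latest date, not an actual one. The analysis plan, the full protocol or the registry record may already settle these points, and the article describes the plan as detailing analyses, not as setting criteria. This limits what can be claimed: nothing shows that a reading has been or will be chosen late. It does not remove the contradictions in the published text, and nothing in that text requires them to be settled before the counts are known.

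Finally, the contradictions need reconciling whatever the deadline. That is true. The deadline adds a reason to do it now and to record what was known.

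**Conclusion.** The point holds in a limited form and merits a change. The stated deadline allows the consent share to be known to within one inclusion. Under even recruitment over an assumed 6 to 36 months, it also allows completion and pooled compliance to be known for about 83% to 96% of the planned sample. Allocation blinding does not protect these totals. The exposure covers only the direction and denominator of the consent criterion, the interruption rule, the missing participant-level compliance target, and the completion limit with its gap from 75% to 90%.

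Within that scope the reading can decide the result. The completion conflict at 54 of 60 and the opposite directions of the consent criterion follow from the text alone. The interruption contrast (89% against 16% at 80% nightly use) assumes independent misses and reads the Discussion sentence as a total. It narrows as use rises, to 100% against 95% at 95% use.

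A reader might go further and infer that the feasibility verdict is biased. The article gives no evidence of that, and the deadline is ordinary for the blinded active-versus-sham analyses.

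**What to change.** Issue a dated amendment or registry update now that:
- reconciles Feasibility outcomes, Discontinuation or modification of interventions, and the Discussion on the consent direction and denominator, the interruption rule, and the completion limit at exactly 90%;
- states the share of participants who must comply, and the verdict for completion between 75% and 90%;
- says that the analysis plan may not alter the limits already published under Feasibility outcomes;
- records how many participants had been randomised, and which feasibility counts were known, at its date.

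Which interruption rule to keep is for the investigators; the sections must simply agree. The deadline in Data analysis may stay for the blinded active-versus-sham analyses.

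The cost is a short amendment with no added data collection. The article describes approval by the medicines agency and the ethics committee, so notification to one or both may be needed.
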